#### Other study parameters and methods for additional analyses

All baseline parameters will be compared between groups using either chi-square tests for categorical variables and t-tests, or Mann–Whitney U-tests for continuous variables.

In addition, the surgical substrate (colon *vs* rectum), type of surgery (laparoscopic *vs* open) and use of adjuvant treatment are compared between groups using chi-square tests.

### Oversight and monitoring

#### Composition of the coordinating center and trial steering committee

The data management team consists of local investigators and local data managers.

#### Composition of the data monitoring committee, its role and reporting structure

There will be a research coordinator at each hospital to monitor the trial.

#### Plans for communicating important protocol amendments to relevant parties (e.g. trial participants, ethics committees)

Important protocol modifications will be communicated by e-mail to all relevant parties.

### Ethics and disseminations

#### Dissemination policy

The results of this study will be communicated to all participating hospitals and published in peer-reviewed journals. In addition, the results will be presented at gynecological and surgical conferences.

#### Plans to give access to the full protocol, participant-level data, and statistical code

Not available.

## Discussion

Up until 2019, there was no explicit focus on the role of the ovaries in CRC patients. In our view, however, patients with CRC could gain a benefit from PSO. Apart from the possibility of developing metastases in the ovaries, the risk of developing ovarian cancer at a later stage in life makes PSO a highly relevant issue.

The outcomes of this study will result in continued discussion of the role of PSO. It should also increase awareness among surgeons for the ovaries and salpinges and stimulate them to check the ovaries for possible abnormalities.

In the case of successful completion of this study, evidence should be obtained on different aspects of ovarian malignancies in CRC patients and on the clinical consequences of prophylactic surgery. We will be able to evaluate the impact of recurrent colorectal malignancy, particularly intra-abdominal, as well as the occurrence (or prevention) of ovarian cancer. In addition, we will gain further insights into the disease-free and overall survival of postmenopausal patients with CRC. Based on this new information, we should be able to conclude whether offering PSO to all postmenopausal patients with CRC is beneficial for their oncologic outcome. This conclusion could eventually be incorporated into the CRC guidelines.

Finally, we will gain insight into the long-term effects of both of these operating strategies (PSO or no PSO) on patient quality of life and on complications. Only then will it be possible to balance the considerations that allow informed individual decision-making on this specific issue.

Within the selected hospitals that have altered their CRC care pathway, younger or premenopausal patients are excluded. Therefore, no conclusions can be drawn for this specific group. Since OM appears to be more prevalent in premenopausal patients, research into the effects of PSO on the oncologic outcome of these patients would also be valuable. However, for such a study to be considered, more comprehensive informed consent should be obtained due to the consequences of surgically induced menopause.

At last, the added value of PSO in patients that developed CRC caused by Lynch syndrome, which is the case in approximately 2–4% of all CRC patients [46, 47], remains unanswered by the current study. Although, it is expected that the number needed to treat in this specific population is a lot smaller compared with the general population, because of a lifetime risk of 3–14% for the development of ovarian cancer in patients with Lynch syndrome [48]. A separate substudy regarding this specific population is therefore in preparation.

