### Explanation for the choice of comparators and efficacy of PSO

The primary goal of implementing PSO is to improve the health of individual women by preventing the development of ovarian malignancies (primary or metastatic), thus improving disease-free survival, preventing additional treatment-related morbidity, and ultimately improving overall survival. As such, PSO could potentially be a cost-effective procedure, especially from an oncological point of view [26].

Fear of cancer recurrence is an important issue for CRC survivors [33]. A patients’ ability to choose additional prophylactic surgery could be helpful in reducing their fear, since the risk of subsequent metastatic or primary ovarian cancer is removed. Moreover, this supports the practice of “shared decision making”. Beginning in 2020, counseling for PSO (preference of “yes” or “no” to PSO) started to be implemented in the CRC care pathway in several Dutch hospitals. Consequently, the impact of PSO can be prospectively evaluated.

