### Randomization, blinding and treatment allocation

Because this study will evaluate the effects of PSO that are facilitated by an altered CRC care pathway, randomization and blinding are not applicable. The two different patient groups are formed based on patient preferences.

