### Sample size

The primary study outcome is the occurrence of either CRC metastases in the ovaries or primary ovarian cancer within 3 years after resection of the (primary) colorectal tumor. Based on previous studies, we assume the incidence of synchronous and metachronous colorectal metastases in the ovaries will be 2.0% during the follow-up period [15, 17, 21]. The incidence of primary ovarian cancer is expected to be 0.1% in this period [39]. This gives an overall incidence of 2.1% in cases where PSO is not performed (non-PSO group).

Following PSO, colorectal tumors can no longer metastasize to the ovaries, while the incidence of primary ovarian malignancy should presumably be 0% (PSO group). However, a small risk of primary ovarian malignancy still exists after PSO due to the development of ‘ovarian remnant syndrome’ (ORS) [40–42]. This risk is estimated to be approximately 0.01% for the PSO group.

Based on these assumptions and an alfa of 0.05 with power of 80%, a sample size calculation was performed using an online sample size calculator for comparison of two proportions [43]. This gave a sample size of 371 patients per group, or 742 in total.

Since all eligible patients are not randomized, it is necessary to correct for possible confounders. According to the one-in-ten rule, at least 10 events (of ovarian malignancies) are needed per factor studied in order to achieve sufficient statistical power [44]. Besides PSO, correction will also be made for age as another possible confounder.

Based on current clinical practice, we estimate that about half of all postmenopausal CRC patients undergo PSO during resection of their colorectal tumor. Therefore, we expect the two study groups to be approximately equal in size. The estimated incidence of ovarian malignancies in the total study population will thus be 1.055% (average of 2.1% and 0.01%), thus requiring a sample size of at least 1896 patients (20/0.01055).

Finally, after taking into account a dropout rate of 5%, at least 1996 patients should be recruited into the study.

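### On the protocol's own figures PSO can raise 3-year disease-free survival by only about 2 points through ovarian prevention, so the DFS and OS comparisons cannot support the planned conclusion on oncologic outcome

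*Protocol article*

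**What the plan says.** All references are to the protocol article.

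- **Route of benefit.** The section explaining the choice of comparators says PSO is to help "by preventing the development of ovarian malignancies (primary or metastatic), thus improving disease-free survival", and in the end overall survival (OS).
- **Size of the ovarian effect.** Under Sample size: "This gives an overall incidence of 2.1% in cases where PSO is not performed (non-PSO group"). For women who have PSO: "This risk is estimated to be approximately 0.01% for the PSO group". The window is "within 3 years after resection of the (primary) colorectal tumor".
- **Group formation.** "The two different patient groups are formed based on patient preferences". On numbers, "we expect the two study groups to be approximately equal in size".
- **DFS analysis.** The statistical section on the primary study parameters compares 3-year DFS by Kaplan-Meier curves and the log-rank test. Cox regression follows if baseline variables differ. Five-year OS is a secondary objective.
- **Covariates.** The sample size names age as the confounder to be corrected for. Table 2 lists age, ASA class, BMI, earlier oophorectomy, comorbidities and neo-adjuvant therapy, but not tumour stage. pTNM and adjuvant treatment are collected as other study parameters.
- **Conclusion.** After mentioning ovarian malignancy, intra-abdominal relapse, DFS and OS, the Discussion says that "we should be able to conclude whether offering PSO to all postmenopausal patients with CRC is beneficial for their oncologic outcome". It states no limit from confounding or from the small possible effect.

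**The concern.** If PSO acts on DFS by removing ovarian events, its effect on DFS cannot exceed the number of ovarian events available to remove. On the protocol's figures that is about 2 in 100 women. All other relapses and deaths enter the DFS comparison as well, and they depend on stage, fitness and adjuvant treatment. Women who accept extra surgery may differ from women who decline it on each of these.

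The comparison is therefore asked to show a small effect against a background where imbalance between self-selected groups could be of similar size. If a clear DFS or OS difference appeared, the Discussion as written would allow it to be read as a benefit of PSO and passed on to guidelines. If none appeared, it could be read as evidence against a benefit that the study was too small to see.

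**Working it through.** **Inputs from the document.** Ovarian malignancy 2.1% without PSO and 0.01% with PSO over 3 years; 371 per group; 1896 analysed; 1996 recruited; groups about equal, so 1896/2 = 948 per group. **Assumed:** 3-year DFS without PSO of 60-85%. The only DFS levels in the document are 5-year figures from the earlier randomised study (78% vs 68%).

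**1. The plan's own sample size.** Two-sided alpha 0.05, 80% power, unpooled variance:
n = (1.960 + 0.842)² × (0.021 × 0.979 + 0.0001 × 0.9999) / 0.0209² = 371. This matches. 20/0.01055 = 1896 and 1896/0.95 = 1996 also match.

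**2. Ceiling on the DFS gain.** 2.1% − 0.01% = 2.09 points. It is reached only if every prevented ovarian malignancy would have been that patient's only DFS event. If half of them would have relapsed or died anyway, the gain is 2.09 × 0.5 = about 1.0 point. With the literature mean of 3.4% from the Introduction in place of 2.0%, the ceiling is 3.4 + 0.1 − 0.01 = about 3.5 points.

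**3. Precision and power, with no confounding.** SE = √[(p₁(1 − p₁) + p₂(1 − p₂))/948], where p₂ = p₁ + 0.0209. At p₁ = 0.68: √[(0.2176 + 0.2096)/948] = 0.0212, and 1.96 × 0.0212 = 4.2 points.

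| Assumed DFS without PSO | 95% CI half-width (points) | Power for 2.09 points | Power for 3.49 points |
|---|---|---|---|
| 60% | 4.4 | 15% | 35% |
| 68% | 4.2 | 17% | 38% |
| 75% | 3.8 | 19% | 44% |
| 80% | 3.5 | 21% | 50% |
| 85% | 3.1 | 26% | 61% |

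The 2.09-point ceiling lies inside the half-width throughout. The 3.5-point alternative lies inside it up to 75%, is level with it at 80% and exceeds it at 85%. For 80% power at 2.09 points, about 4,300 (DFS 85%) to 8,500 (DFS 60%) per group would be needed.

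**4. What selection could do (illustration, all inputs assumed).** Bias before adjustment = imbalance in a factor × DFS gap between its levels. To create 2.09 points, a factor with a 20-point gap needs an imbalance of 2.09/20 = 10.5 points; a 10-point gap needs 21, and a 30-point gap needs 7. With no PSO effect, a residual bias of 3 points would give p < 0.05 in 29-39% of studies, and 5 points in 67-82% (DFS 68-80%).

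**5. Overall survival, indicative only.** Five-year survival with ovarian metastases is given as 12-27%. If every prevented case then survived 5 years, the gain is 2.09 × (1 − 0.27) = 1.5 to 2.09 × (1 − 0.12) = 1.8 points. This applies a 3-year incidence to 5-year survival and omits ovarian events in years 3 to 5, so it is not a strict maximum.

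**6. The ovarian endpoint.** With 948 per group, power for 2.1% vs 0.01% is about 99%.

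**The case against.** **The Discussion does not rest on DFS and OS alone.** It mentions ovarian malignancy and intra-abdominal relapse first, and the primary objective, Table 1 and the sample size all concern ovarian malignancy. This stands. But DFS is also the endpoint analysed under the primary study parameters, and the concluding sentence speaks of oncologic outcome in general.

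**Adjustment is planned.** Cox regression is specified, pTNM and adjuvant treatment are collected, and intra-abdominal relapse and primary ovarian cancer are compared separately. So it would be wrong to infer that nothing addresses selection. What remains is narrower. Adjustment depends on observed baseline differences, Table 2 omits stage, the text does not say whether pTNM enters the model, and the site-specific analyses are not used to detect selection.

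**The size of selection is unknown.** A reader might infer that a significant DFS result would more likely reflect selection than PSO. The document gives neither size nor direction of selection, so only *could* is justified.

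**Other routes exist.** The section on consequences of PSO lists reduced recurrence as a benefit and describes a hormonal influence. So PSO is not shown to be incapable of a larger effect; the ceiling applies to ovarian prevention. No figure is given for any other route.

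**A null result is informative.** A half-width of about 4.2 points around zero would exclude a gap as large as the 10 points in the earlier randomised study. It would not exclude 2 points.

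**Splitting DFS by component has little power for a bias of about 2 points.** This is true, and a null there is not reassurance. The split helps most with a large difference. At DFS 68%, a significant result needs about 4.2 points, of which ovarian events can supply at most about 2.1; of a 10-point gap, about 8 would have to be non-ovarian.

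**Conclusion.** The point holds in this form. Through ovarian prevention, the protocol's figures allow at most about 2.1 points of 3-year DFS, or about 3.5 with the higher literature incidence. With about 948 per group, the 2.1-point effect lies inside the confidence interval half-width (4.2 points at DFS 68%; 3.1-4.4 over the assumed 60-85%), with about 15-26% power. Residual selection between preference-formed groups could produce a difference of this size or larger; whether it will cannot be said from the document.

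A DFS difference well above 2 points therefore could not be attributed to ovarian prevention, and a null result could rule out large effects but not the posited one. The DFS and OS comparisons do not support the stated conclusion on oncologic outcome. The ovarian malignancy comparison is not short of numbers on the same assumptions.

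The 2.1-point ceiling uses the protocol's incidences. The precision and power figures rest on the assumed DFS level and equal groups, and the selection figures are illustrative.

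**What to change.** 1. **Split DFS by first event:** ovarian relapse, non-ovarian relapse, and death without relapse. Fit the same Cox model as for overall DFS to each. State in advance that a group difference in the non-ovarian components will be read as possible residual selection and not as an effect of PSO. Death without relapse is the cleaner control, because the protocol mentions recurrence and hormonal routes that could touch non-ovarian relapse. State also that finding no difference does not prove absence of selection.
2. **Reword the Discussion** so that the conclusion rests on ovarian malignancy and its NNT. Describe DFS and OS as observational associations whose plausible effect through ovarian prevention is about 2 points at most.

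Cost: one or two extra models on recurrence and survival data already being collected, some wording, and a more modest stated conclusion.

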## Data Availability

The datasets and/or analyzed data will be available from the principal investigator (RR) on reasonable request. The Data Management plan and Trial Master File are managed by the principal investigator (RR). Identifying/confidential patient data will not be shared.

## Abbreviations

ASA: American Society of Anesthesiologists
BMI: Body Mass Index
CRC: Colorectal Cancer
DFS: Disease-free survival
EORTC: European Organization for Research and Treatment of Cancer European Union
HRQL: Health-related quality of life
IC: Informed Consent
METC: Medisch ethische toetsing commissie (*dutch*), translation: Medical research ethics committee (MREC)
NNT: Number Needed to Treat
OM: Ovarian Metastases
PSO: Prophylactic (bilateral) salpingo-oophorectomy
pTNM: Pathological Tumor-Node-Metastasis
QLQ: Quality of Life Questionnaire
ROMIC: Role of Ovarian Metastases In Colorectal cancer
WMO: Wet Medisch-wetenschappelijk Onderzoek (*dutch*), translation: Medical Research Involving Human Subjects Act
